**8.1.A. Moderate exacerbation**

**1. New Sequence**

- 1.1. The occurrence of [**Continuous prednisone (14D)**](https://bwh-dope.aetion.com/measures/details/603159/1495/0/basics), starting at least one day after the cohort entry date; and
- 1.2. The occurrence of [**COPD hospitalization (COPD codes, primary)**](https://bwh-dope.aetion.com/measures/details/603148/1495/0/basics), not occurring within 14 days before the start of 1.1, and until 14 days after the end of 1.1.

The event of interest in this group is 1.1.

NOTE: Below are further definitions of terms used to construct the moderate exacerbation definition.

[**Continuous**](https://bwh-dope.aetion.com/measures/details/603159/1495/0/basics) **prednisone (14D) is is defined as:**

[**Prednisone fill**](https://bwh-dope.aetion.com/measures/details/603156/1495/0/basics), with an allowed gap of 14 days and an episode extension of 0 days.

**COPD hospitalization (COPD codes, primary)** is defined as:

- The occurrence of **Inpatient Confinement** with the following attributes:
  - **Diagnosis Code (Primary Position), ICD-9** is any of: { “491”, “491.0”, “491.1”, “491.21”, “491.22”, “491.8”, “491.9”, “492”, “492.0”, “492.8”, “496” }
    - 491 - CHRONIC BRONCHITIS
    - 491.0 - SIMPLE CHRONIC BRONCHITIS
    - 491.1 - MUCOPURULENT CHRONIC BRONCHITIS
    - 491.21 - OBSTRUCTIVE CHRONIC BRONCHITIS WITH (ACUTE) EXACERBATION
    - 491.22 - OBSTRUCTIVE CHRONIC BRONCHITIS WITH ACUTE BRONCHITIS
    - 491.8 - OTHER CHRONIC BRONCHITIS
    - 491.9 - UNSPECIFIED CHRONIC BRONCHITIS
    - 492 - EMPHYSEMA
    - 492.0 - EMPHYSEMATOUS BLEB
    - 492.8 - OTHER EMPHYSEMA
    - 496 - CHRONIC AIRWAY OBSTRUCTION NOT ELSEWHERE CLASSIFIED
- The occurrence of **Inpatient Confinement** with the following attributes:
  - **Diagnosis Code (Primary Position), ICD-10** is any of: { “J41.0”, “J41.1”, “J41.8”, “J43.0”, “J43.1”, “J43.2”, “J43.8”, “J43.9”, “J44.0”, “J44.1”, “J44.9”, “J42”, “J41”, “J43”, “J44” }
    - J41.0 - Simple chronic bronchitis
    - J41.1 - Mucopurulent chronic bronchitis
    - J41.8 - Mixed simple and mucopurulent chronic bronchitis
    - J43.0 - Unilateral pulmonary emphysema [MacLeod's syndrome]
    - J43.1 - Panlobular emphysema
    - J43.2 - Centrilobular emphysema
    - J43.8 - Other emphysema
    - J43.9 - Emphysema, unspecified
    - J44.0 - Chronic obstructive pulmonary disease with acute lower respiratory infection
    - J44.1 - Chronic obstructive pulmonary disease with (acute) exacerbation
    - J44.9 - Chronic obstructive pulmonary disease, unspecified
    - J42 - Unspecified chronic bronchitis
    - J41 - Simple and mucopurulent chronic bronchitis
    - J43 - Emphysema
    - J44 - Other chronic obstructive pulmonary disease

**8.1.B. Severe COPD exacerbation**

This measure identifies continuous days that the following measure has:

[**Severe COPD exacerbation (14D, COPD codes primary) w/out specifying allowable gap /w severe episodes**](https://bwh-dope.aetion.com/measures/details/603154/1495/0/basics), with an allowed gap of 14 days and an episode extension of 0 days.

This measure creates a flag that is true on the days that are identified:

- [**COPD hospitalization and NO continuous prednisone in prior 14 days (COPD codes primary)**](https://bwh-dope.aetion.com/measures/details/603152/1495/0/basics)
- [**COPD hospitalization w/in 14D of continuous prednisone (COPD codes, primary)**](https://bwh-dope.aetion.com/measures/details/603151/1495/0/basics)

NOTE: Below are further definitions of terms used to construct the moderate exacerbation definition.

- [**COPD hospitalization and NO continuous prednisone in prior 14 days (COPD codes primary)**](https://bwh-dope.aetion.com/measures/details/603152/1495/0/basics)

This measure was defined as:

**1. New Sequence**

- 1.1. The occurrence of [**COPD hospitalization (COPD codes, primary)**](https://bwh-dope.aetion.com/measures/details/603148/1495/0/basics); and
- 1.2. The occurrence of [**Continuous prednisone (14D)**](https://bwh-dope.aetion.com/measures/details/603159/1495/0/basics), not occurring within 14 days before the start of 1.1, and until 0 days before the start of 1.1.

The event of interest in this group is 1.1.

- [**COPD hospitalization w/in 14D of continuous prednisone (COPD codes, primary)**](https://bwh-dope.aetion.com/measures/details/603151/1495/0/basics)

This measure was defined as:

**1. New Sequence**

- 1.1. The occurrence of [**Continuous prednisone (14D)**](https://bwh-dope.aetion.com/measures/details/603159/1495/0/basics); and
- 1.2. The occurrence of [**COPD hospitalization (COPD codes, primary)**](https://bwh-dope.aetion.com/measures/details/603148/1495/0/basics), starting within 0 days after the start of 1.1, and until 14 days after the end of 1.1.

The event of interest in this group is 1.1.

**8.1.C. Moderate or Severe COPD Exacerbation**

This measure creates a flag that is true on the days that are identified:

- [**Moderate COPD exacerbation (14D, COPD codes primary)**](https://bwh-dope.aetion.com/measures/details/603153/1495/0/basics) as defined in 8.1.A above.
- [**Severe COPD exacerbation (14D, COPD codes primary) specifying 14D allowable gap**](https://bwh-dope.aetion.com/measures/details/603160/1495/0/basics) as defined in 8.1.B. above.

**Primary safety outcome: First hospitalization for pneumonia**

We will allow a pneumonia diagnosis in any position in our prior work since this is an acute condition (and we can be confident that, if somebody has a pneumonia diagnosis during a hospitalization, he/she is experiencing an acute process—which stands in contrast to a COPD diagnosis in any position during the hospitalization, where we cannot be sure that this is an acute process). The full codes for pneumonia hospitalizations are below and have been validated with a PPV of 0.88 (95% CI 0.82-0.92)^5^ using ICD-9 codes. We converted ICD-9 codes to ICD-10 codes using clinical review, because our study period was after the transition to using ICD-10 codes in the United States.

This event measure was defined as occurring when any of the following criteria were met:

- The occurrence of **Inpatient Confinement** with the following attributes:
  - **Diagnosis Code (Any Confinement Position), ICD-9** is any of: { “480”, “480.0”, “480.1”, “480.2”, “480.3”, “480.8”, “480.9”, “481”, “482”, “482.0”, “482.1”, “482.2”, “482.3”, “482.30”, “482.31”, “482.32”, “482.39”, “482.4”, “482.40”, “482.41”, “482.42”, “482.49”, “482.8”, “482.81”, “482.82”, “482.83”, “482.84”, “482.89”, “482.9”, “483”, “483.0”, “483.1”, “483.8”, “484”, “484.1”, “484.3”, “484.5”, “484.6”, “484.7”, “484.8”, “485”, “486”, “487.0”, “488.01”, “488.11”, “488.81” }
    - 480 - VIRAL PNEUMONIA
    - 480.0 - PNEUMONIA DUE TO ADENOVIRUS
    - 480.1 - PNEUMONIA DUE TO RESPIRATORY SYNCYTIAL VIRUS
    - 480.2 - PNEUMONIA DUE TO PARAINFLUENZA VIRUS
    - 480.3 - PNEUMONIA DUE TO SARS-ASSOCIATED CORONAVIRUS
    - 480.8 - PNEUMONIA DUE TO OTHER VIRUS NOT ELSEWHERE CLASSIFIED
    - 480.9 - VIRAL PNEUMONIA UNSPECIFIED
    - 481 - PNEUMOCOCCAL PNEUMONIA [STREPTOCOCCUS PNEUMONIAE PNEUMONIA]
    - 482 - OTHER BACTERIAL PNEUMONIA
    - 482.0 - PNEUMONIA DUE TO KLEBSIELLA PNEUMONIAE
    - 482.1 - PNEUMONIA DUE TO PSEUDOMONAS
    - 482.2 - PNEUMONIA DUE TO HEMOPHILUS INFLUENZAE (H. INFLUENZAE)
    - 482.3 - PNEUMONIA DUE TO STREPTOCOCCUS
    - 482.30 - PNEUMONIA DUE TO STREPTOCOCCUS UNSPECIFIED
    - 482.31 - PNEUMONIA DUE TO STREPTOCOCCUS GROUP A
    - 482.32 - PNEUMONIA DUE TO STREPTOCOCCUS GROUP B
    - 482.39 - PNEUMONIA DUE TO OTHER STREPTOCOCCUS
    - 482.4 - PNEUMONIA DUE TO STAPHYLOCOCCUS
    - 482.40 - PNEUMONIA DUE TO STAPHYLOCOCCUS UNSPECIFIED
    - 482.41 - METHICILLIN SUSCEPTIBLE PNEUMONIA DUE TO STAPHYLOCOCCUS AUREUS
    - 482.42 - METHICILLIN RESISTANT PNEUMONIA DUE TO STAPHYLOCOCCUS AUREUS
    - 482.49 - OTHER STAPHYLOCOCCUS PNEUMONIA
    - 482.8 - PNEUMONIA DUE TO OTHER SPECIFIED BACTERIA
    - 482.81 - PNEUMONIA DUE TO ANAEROBES
    - 482.82 - PNEUMONIA DUE TO ESCHERICHIA COLI [E.COLI]
    - 482.83 - PNEUMONIA DUE TO OTHER GRAM-NEGATIVE BACTERIA
    - 482.84 - PNEUMONIA DUE TO LEGIONNAIRES' DISEASE
    - 482.89 - PNEUMONIA DUE TO OTHER SPECIFIED BACTERIA
    - 482.9 - BACTERIAL PNEUMONIA UNSPECIFIED
    - 483 - PNEUMONIA DUE TO OTHER SPECIFIED ORGANISM
    - 483.0 - PNEUMONIA DUE TO MYCOPLASMA PNEUMONIAE
    - 483.1 - PNEUMONIA DUE TO CHLAMYDIA
    - 483.8 - PNEUMONIA DUE TO OTHER SPECIFIED ORGANISM
    - 484 - PNEUMONIA IN INFECTIOUS DISEASES CLASSIFIED ELSEWHERE
    - 484.1 - PNEUMONIA IN CYTOMEGALIC INCLUSION DISEASE
    - 484.3 - PNEUMONIA IN WHOOPING COUGH
    - 484.5 - PNEUMONIA IN ANTHRAX
    - 484.6 - PNEUMONIA IN ASPERGILLOSIS
    - 484.7 - PNEUMONIA IN OTHER SYSTEMIC MYCOSES
    - 484.8 - PNEUMONIA IN OTHER INFECTIOUS DISEASES CLASSIFIED ELSEWHERE
    - 485 - BRONCHOPNEUMONIA ORGANISM UNSPECIFIED
    - 486 - PNEUMONIA ORGANISM UNSPECIFIED
    - 487.0 - INFLUENZA WITH PNEUMONIA
    - 488.01 - INFLUENZA DUE TO IDENTIFIED AVIAN INFLUENZA VIRUS WITH PNEUMONIA
    - 488.11 - INFLUENZA DUE TO IDENTIFIED 2009 H1N1 INFLUENZA VIRUS WITH PNEUMONIA
    - 488.81 - INFLUENZA DUE TO IDENTIFIED NOVEL INFLUENZA A VIRUS WITH PNEUMONIA
- The occurrence of **Inpatient Confinement** with the following attributes:
  - **Diagnosis Code (Any Confinement Position), ICD-10** is any of: { “J09.X1”, “J10.0”, “J10.00”, “J10.01”, “J10.08”, “J11.0”, “J11.00”, “J11.08”, “J12”, “J12.0”, “J12.1”, “J12.2”, “J12.3”, “J12.8”, “J12.81”, “J12.89”, “J12.9”, “J13”, “J14”, “J15”, “J15.0”, “J15.1”, “J15.2”, “J15.20”, “J15.21”, “J15.211”, “J15.212”, “J15.29”, “J15.3”, “J15.4”, “J15.5”, “J15.6”, “J15.7”, “J15.8”, “J15.9”, “J16”, “J16.0”, “J16.8”, “J17”, “J18”, “J18.0”, “J18.1”, “J18.2”, “J18.8”, “J18.9”, “A01.03”, “A02.22”, “A37.01”, “A37.11”, “A37.81”, “A37.91”, “A54.84”, “B01.2”, “B05.2”, “B06.81”, “B77.81”, “J85.1”, “J22” }
    - J09.X1 - Influenza due to identified novel influenza A virus with pneumonia
    - J10.0 - Influenza due to other identified influenza virus with pneumonia
    - J10.00 - Influenza due to other identified influenza virus with unspecified type of pneumonia
    - J10.01 - Influenza due to other identified influenza virus with the same other identified influenza virus pneumonia
    - J10.08 - Influenza due to other identified influenza virus with other specified pneumonia
    - J11.0 - Influenza due to unidentified influenza virus with pneumonia
    - J11.00 - Influenza due to unidentified influenza virus with unspecified type of pneumonia
    - J11.08 - Influenza due to unidentified influenza virus with specified pneumonia
    - J12 - Viral pneumonia, not elsewhere classified
    - J12.0 - Adenoviral pneumonia
    - J12.1 - Respiratory syncytial virus pneumonia
    - J12.2 - Parainfluenza virus pneumonia
    - J12.3 - Human metapneumovirus pneumonia
    - J12.8 - Other viral pneumonia
    - J12.81 - Pneumonia due to SARS-associated coronavirus
    - J12.89 - Other viral pneumonia
    - J12.9 - Viral pneumonia, unspecified
    - J13 - Pneumonia due to Streptococcus pneumoniae
    - J14 - Pneumonia due to Hemophilus influenzae
    - J15 - Bacterial pneumonia, not elsewhere classified
    - J15.0 - Pneumonia due to Klebsiella pneumoniae
    - J15.1 - Pneumonia due to Pseudomonas
    - J15.2 - Pneumonia due to staphylococcus
    - J15.20 - Pneumonia due to staphylococcus, unspecified
    - J15.21 - Pneumonia due to staphylococcus aureus
    - J15.211 - Pneumonia due to Methicillin susceptible Staphylococcus aureus
    - J15.212 - Pneumonia due to Methicillin resistant Staphylococcus aureus
    - J15.29 - Pneumonia due to other staphylococcus
    - J15.3 - Pneumonia due to streptococcus, group B
    - J15.4 - Pneumonia due to other streptococci
    - J15.5 - Pneumonia due to Escherichia coli
    - J15.6 - Pneumonia due to other Gram-negative bacteria
    - J15.7 - Pneumonia due to Mycoplasma pneumoniae
    - J15.8 - Pneumonia due to other specified bacteria
    - J15.9 - Unspecified bacterial pneumonia
    - J16 - Pneumonia due to other infectious organisms, not elsewhere classified
    - J16.0 - Chlamydial pneumonia
    - J16.8 - Pneumonia due to other specified infectious organisms
    - J17 - Pneumonia in diseases classified elsewhere
    - J18 - Pneumonia, unspecified organism
    - J18.0 - Bronchopneumonia, unspecified organism
    - J18.1 - Lobar pneumonia, unspecified organism
    - J18.2 - Hypostatic pneumonia, unspecified organism
    - J18.8 - Other pneumonia, unspecified organism
    - J18.9 - Pneumonia, unspecified organism
    - A01.03 - Typhoid pneumonia
    - A02.22 - Salmonella pneumonia
    - A37.01 - Whooping cough due to Bordetella pertussis with pneumonia
    - A37.11 - Whooping cough due to Bordetella parapertussis with pneumonia
    - A37.81 - Whooping cough due to other Bordetella species with pneumonia
    - A37.91 - Whooping cough, unspecified species with pneumonia
    - A54.84 - Gonococcal pneumonia
    - B01.2 - Varicella pneumonia
    - B05.2 - Measles complicated by pneumonia
    - B06.81 - Rubella pneumonia
    - B77.81 - Ascariasis pneumonia
    - J85.1 - Abscess of lung with pneumonia
    - J22 - Unspecified acute lower respiratory infection

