**Part 2: Protocol**

Protocol Version Date: 3/4/2024

Author(s): [name], [name], [name], [name], [name]

1. **Title:** The comparative effectiveness and safety of fluticasone-salmeterol via metered-dose vs. dry powder inhalers in COPD
2. **Core Research Team:** [name], [name], [name], [name], [name] (Implementation in the Aetion Evidence Platform: [name]; PI: [name])
3. **Aim(s)**

**Aim 1 (effectiveness):** To compare new users of fluticasone-salmeterol via metered-dose vs. dry powder inhalers on the outcome of first moderate or severe COPD exacerbation.

**Aim 2 (safety)**: To compare new users of fluticasone-salmeterol via metered-dose vs. dry powder inhalers on the outcome of first pneumonia hospitalization.

1. **Data source**: Optum Clinformatics claims database January 1, 2007-November 30, 2023. The study will begin in 2007 since that is the first full year after Advair HFA was approved (Advair Diskus was approved in 2000). Thus, both products were on the US market throughout the study period.
2. **Study Design Diagram:** see Appendix Figure 1
3. **Cohort Identification**

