| 9 | Cohort entry between 2019-2023 | This study period includes both the approval of the first generic fluticasone-salmeterol (Wixela Inhub) in 2019, as well as the COVID-19 pandemic (starting in 2020). These events could potentially confound our estimate of the ATE due to changes in treatment selection, as well as respiratory outcomes, care, and hospitalizations due to COVID-19. | Allows us to observe how the ATE changes relative to our overall estimate during a period that includes COVID-19 and a major generic approval, which could flag potential confounding in the overall cohort. | Changes in ATE are likely due to unobserved confounders rather than comparative intrinsic effectiveness/safety between the Advair devices. |
| 10 | Gender (Male/Female) | COPD severity, incidence, and care has been observed to vary across various demographic dimensions; large observational studies such as this allow us to observe patients who are often excluded from clinical trials.^22–26^ | Allows us to observe potential heterogenous treatment effects between different demographic groups that often have inadequate representation in RCTs. | None. |
| 11 | Race (White/Black/  Hispanic/Asian) |  |  |  |
| 12 | Age (less than 65 vs. 65 and older) |  |  |  |

*Each subgroup analysis will be performed with patients who meet the definition (for example, at least 1 baseline COPD exacerbation) and those who do not meet the definition (for example, no baseline COPD exacerbations).

1. **Sensitivity analyses**

|  | **Sensitivity** | **Why?** | **Strengths** | **Weaknesses** |
| --- | --- | --- | --- | --- |
| **1** | Alter the grace period for continuous use (30 days, 90 days). | This allows us to assess whether estimates differ when the exposure definition changes. | Using a shorter grace period (30 days) will provide more specificity with respect to the exposure while the longer grace period (90 days) will better reflect real-world practice. | 30-day grace period will exclude people who are truly exposed, while 90-day grace period will include people are not truly exposed |
| **2** | ITT over one year of follow-up | We will assess whether there are differences between Advair Diskus and Advair HFA in a truly real-world setting in which patients frequently discontinue therapy. | This analysis will allow us to avoid informative censoring. | Much of the included person-time will be unexposed person-time. |

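### The ICD-9 and ICD-10 code lists for the primary safety outcome do not cover the same conditions, and neither names COVID-19 pneumonia, so the outcome depends on calendar period

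*Protocol*

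**What the plan says.** Under the heading for the primary safety outcome, the protocol counts an inpatient confinement carrying any code from an ICD-9 list or an ICD-10 list, in any diagnosis position. It reports a PPV of 0.88 (95% CI 0.82 to 0.92), obtained with ICD-9 codes, and then explains where the ICD-10 list came from: "We converted ICD-9 codes to ICD-10 codes using clinical review, because our study period was after the transition to using ICD-10 codes".

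The data source item in Part 2 gives the period as "Optum Clinformatics claims database January 1, 2007-November 30, 2023".

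The ICD-9 list includes "482.84 - PNEUMONIA DUE TO LEGIONNAIRES' DISEASE" and "480.3 - PNEUMONIA DUE TO SARS-ASSOCIATED CORONAVIRUS". The ICD-10 list includes "J12.81 - Pneumonia due to SARS-associated coronavirus" and "J12.89 - Other viral pneumonia". Row 9 of the subgroup table (cohort entry 2019 to 2023) recognises that the estimate could be affected by changes in "respiratory outcomes, care, and hospitalizations due to COVID-19".

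**The concern.** When an outcome is assembled from two coding systems over one continuous study period, the two lists should describe the same set of conditions. Otherwise an admission of the same kind is an event in one calendar period and not in another. Here the stated reason for the conversion treats the study as if only ICD-10 mattered, which may be why the lists were not reconciled.

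The primary safety outcome, and the secondary annual rate of pneumonia hospitalizations that rests on it, would then mean different things in different years. Events would be lost, event rates would not be comparable across periods, and the 2019 to 2023 safety result would be harder to read. Those are the years in which the protocol itself expects COVID-19 to matter.

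**Working it through.** The plan states no figure to reproduce. The check compares the two lists by code and by label.

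**1. Which lists are in use.** The period runs from 1 January 2007 to 30 November 2023. The protocol does not date the ICD-10 transition. A live ICD-9 criterion is useful only if part of the period precedes it. The statement that the study period came after the transition therefore conflicts with the 2007 start and with the ICD-9 list in the same section.

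**2. Size of the lists.** ICD-9: 46 codes. ICD-10: 58 codes.

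**3. Conditions side by side.**

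| Condition | ICD-9 list | ICD-10 list |
| --- | --- | --- |
| Legionnaires' pneumonia | 482.84 | no label names it |
| Pneumonia in cytomegalic inclusion disease, anthrax, aspergillosis, other systemic mycoses | 484.1, 484.5, 484.6, 484.7 | at most the residual J17 |
| Pneumonia in whooping cough | 484.3 | A37.01, A37.11, A37.81, A37.91 |
| Lower respiratory infection, unspecified | no label | J22 |
| Lung abscess with pneumonia | no label | J85.1 |
| SARS-associated coronavirus pneumonia | 480.3 | J12.81 |
| COVID-19 pneumonia | no label | no label |

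The whooping cough row is informative. The conversion gave 484.3 four cause-specific codes instead of leaving it to J17, but its neighbours 484.1 and 484.5 to 484.7 received none. The remaining infection-specific A and B codes in the ICD-10 list can be read as falling under the ICD-9 residual 484.8. J22 and J85.1 have no such home.

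**4. Matching rule.** The protocol does not say whether codes match exactly or by prefix. If by prefix, the listed parents J12 and J12.8 would capture any COVID-19 sub-code placed beneath them. However, 35 of the 58 ICD-10 codes are children of another listed code and would then be redundant, so the list reads as exact-match. This is an inference, not a stated rule. Under either rule no listed ICD-10 label or parent names Legionnaires' pneumonia.

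**5. Calendar time exposed to the COVID-19 gap.**
- 2007 to 2022: 16 × 365 + 4 leap days = 5,844 days. To 30 November 2023: 5,844 + 334 = 6,178 days.
- 2020 to 30 November 2023: 366 + 365 + 365 + 334 = 1,430 days.
- Share: 1,430 / 6,178 = 0.231, or 23%.

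This is a share of calendar time, not of admissions. A share of events would need the proportion of admissions in those years, the proportion due to COVID-19, and the proportion of those with no other listed code. The documents give none of these.

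**6. Whether another analysis repairs it.** Sensitivity analysis 7 moves the pneumonia diagnosis to the primary position but leaves the codes unchanged. Subgroup row 9 uses the same list. Row 8 (entry 2007 to 2018) largely avoids the pandemic but does not align the two lists.

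**The case against.** Several counter-arguments have force.

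- **Partial capture.** Any diagnosis position counts, and residual codes such as J12.89, J12.9, J15.8 and J18.9 are listed. A COVID-19 or Legionella admission that also carries one of these is still an event. This stands: capture is partial and depends on coding practice. It is not zero.
- **Same list in both arms.** Missed codes lower sensitivity. If the loss does not differ by device, it costs events but need not bias the hazard ratio. Year of cohort entry is in the propensity score model, and row 8 gives a mostly pre-pandemic estimate. A reader might infer that the safety hazard ratio is biased; the documents show no route by which capture would differ between the two inhalers.
- **Purpose of row 9.** A reader might infer that the 2019 to 2023 subgroup becomes uninterpretable. Its stated aim is to see whether the treatment effect shifts and to flag confounding, not to count COVID-19 pneumonia, and it already warns against reading changes as device effects. It is harder to interpret, no more than that.
- **A break within the pandemic.** A reader might suppose that counting changed when COVID-19 pneumonia received its own code. The documents contain no such code and no date for one, so this cannot be argued from them.
- **The PPV.** The protocol discloses that 0.88 comes from ICD-9 codes, so there is no concealment. It still does not validate an ICD-10 list containing J22.
- **Leaving COVID-19 out on purpose.** That would be defensible, but the protocol states no such intention, and the residual codes mean the list would not achieve it.

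**Conclusion.** The point holds in a limited form. The sentence placing the study after the ICD-10 transition is wrong. The two lists differ in both directions: 482.84 has no named ICD-10 counterpart, 484.1 and 484.5 to 484.7 have at most a residual, and J22 and J85.1 have no ICD-9 counterpart. COVID-19 pneumonia is named in neither list, though the data cover 2020 to November 2023 (23% of study days) and SARS-associated coronavirus pneumonia is counted.

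The consequence is a primary safety outcome whose content depends on the calendar period, with some events lost. How many cannot be determined from the documents. Legionnaires' and the 484.x conditions are probably few, and the COVID-19 gap is probably the larger; both are assumptions. The COVID-19 part also assumes exact matching. Bias in the hazard ratio is possible, for example if the device mix shifts over time in a way the weights do not remove, but it is not shown. The change is worth making before analysis because it concerns a primary outcome and is cheap.

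**What to change.** 1. Correct the sentence on the ICD-10 transition to say that the study period uses both coding systems.
2. Add the ICD-10 counterparts of 482.84, 484.1 and 484.5 to 484.7.
3. Either drop J22 and J85.1 or add their ICD-9 counterparts.
4. List the COVID-19 pneumonia code explicitly, and state whether codes match exactly or by prefix.
5. Rerun the pneumonia outcome once without COVID-19-coded admissions, for the full cohort and for the 2019 to 2023 subgroup.

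The cost is a code-list edit and one additional rerun on data already held. The downside is that COVID-19 pneumonias unrelated to the inhaler may enter the main outcome; the rerun would show how much they matter.

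### The ICD-10 code list for the primary safety outcome includes J22, an unspecified lower respiratory infection code, so admissions with no pneumonia code can count as pneumonia

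*Protocol*

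**What the plan says.** Protocol section 8.1, under the primary safety outcome, defines a pneumonia hospitalization as an inpatient confinement carrying any listed ICD-9 or ICD-10 code. On position it says: "We will allow a pneumonia diagnosis in any position in our prior work since this is an acute condition". The reason given is that a pneumonia code during an admission marks something acute, whereas a COPD code may not.

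On validity, the section says the codes "have been validated with a PPV of 0.88 (95% CI 0.82-0.92"), and it attributes that figure to ICD-9 codes. The ICD-10 list is described this way: "We converted ICD-9 codes to ICD-10 codes using clinical review, because our study period was after the transition to using ICD-10 codes".

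Even the unspecified entries in the ICD-9 list are pneumonia codes, for example "486 - PNEUMONIA ORGANISM UNSPECIFIED". The ICD-10 list ends with "J22 - Unspecified acute lower respiratory infection".

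Two other places bear on the point. The COPD hospitalization list in section 8.1.A, which feeds the severe-exacerbation outcome and requires primary position, contains "J44.0 - Chronic obstructive pulmonary disease with acute lower respiratory infection". The data source is given as "Optum Clinformatics claims database January 1, 2007-November 30, 2023".

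**The concern.** The Protocol separates pneumonia (primary safety) from exacerbation (primary effectiveness). A code for an unspecified lower respiratory infection does not make that separation. In a COPD population it can describe an infective exacerbation as readily as a pneumonia.

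Because J22 counts in any position, an admission coded J44.0 first and J22 second meets both primary outcomes although no pneumonia code is present. This route exists only in ICD-10 claims, so the outcome is defined more broadly in the later part of the study than in the earlier part.

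At stake is the specificity of the primary safety outcome. If J22-only admissions are less related to the device than true pneumonias, the hazard ratio is diluted. In a safety comparison, dilution moves the estimate towards no difference, which is the less cautious direction. The annual rate of pneumonia hospitalizations would be affected in the same way if it uses the same list.

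**Working it through.** **1. Content of the lists (counted from section 8.1).**

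| List | Codes | Label names pneumonia | Exceptions |
|---|---|---|---|
| ICD-9 | 46 (all within 480-488) | 46 | none |
| ICD-10 | 58 | 57 | J22 |

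Removing J22 leaves 58 - 1 = 57 ICD-10 codes, all naming pneumonia.

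**2. The overlap route.** An admission with J44.0 primary meets the COPD hospitalization definition in 8.1.A and so the severe-exacerbation outcome. If J22 is a secondary code, the same admission meets the pneumonia definition. With J22 deleted, and no other listed code present, it counts only as an exacerbation.

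**3. The study-period sentence.** It places the study after the change to ICD-10. The data begin on January 1, 2007, and the same section supplies an ICD-9 list for use. Both code systems apply, so the sentence contradicts the rest of the Protocol.

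**4. The stated PPV.** The figure of 0.88 (0.82-0.92) cannot be reproduced, because its numerator and denominator are not given. A Wilson interval around 0.88 rounds to those limits for roughly 140-180 reviewed cases, so the figure is plausible in itself.

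**5. Possible size.** The Protocol gives no J22 frequency, so all inputs here other than the PPV are assumptions.

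*Mixture of two event types.* Let f be the share of counted events that are J22-only. Then, approximately, observed HR = (1 - f) × HR(pneumonia) + f × HR(J22-only).

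- f = 0.05, HR(J22-only) = 1.0: true 1.20 gives 0.95 × 1.20 + 0.05 × 1.0 = 1.190; true 1.30 gives 1.285.
- f = 0.15, HR(J22-only) = 0.9: true 1.20 gives 0.85 × 1.20 + 0.15 × 0.9 = 1.155; true 1.30 gives 1.240.

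*Starting from the stated PPV.* Let s be the J22-only share and q the proportion of those that are true pneumonia, with false events unrelated to treatment. Then PPV = (1 - s) × 0.88 + s × q, and observed HR = PPV × HR + (1 - PPV).

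| s | q | PPV | True 1.20 observed as | True 1.50 observed as |
|---|---|---|---|---|
| 0 | – | 0.880 | 1.176 | 1.440 |
| 5% | 0 | 0.836 | 1.167 | 1.418 |
| 10% | 0 | 0.792 | 1.158 | 1.396 |
| 10% | 0.5 | 0.842 | 1.168 | 1.421 |
| 20% | 0 | 0.704 | 1.141 | 1.352 |

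For a true HR of 1.20, J22 costs 1.176 - 1.158 = 0.018 at a 10% share with no true pneumonias among those events, and 1.176 - 1.141 = 0.035 at 20%. If J22-only events were as reliable as the rest (q = 0.88), the cost would be zero.

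**The case against.** The strongest reply is that the effect may be negligible. Admissions carrying J22 together with a listed pneumonia code add nothing, and nothing in the Protocol shows how often J22 stands alone. Under the assumptions above the shift is small, and the Protocol states no margin that it would cross. All of this stands, and it limits the weight of the point. It does not make J22 a pneumonia code.

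Sensitivity analysis 7 requires the pneumonia code in primary position and so removes the J44.0-first, J22-second admissions. That also stands, but only in part: J22 in primary position would still count, and the primary analysis is unchanged.

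A reader might draw several stronger conclusions that the Protocol does not support:

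- *The any-position rationale fails for J22.* The rationale concerns acuteness, and J22 is an acute diagnosis. The problem is that J22 is not a pneumonia diagnosis.
- *The PPV is claimed for ICD-10 codes.* The Protocol already ties it to ICD-9 codes and says the conversion rested on clinical review.
- *The change of definition confounds the comparison.* Both arms use the same definition at any date, and year of cohort entry is in the propensity score. The 2007-2018 and 2019-2023 subgroups were chosen for generic entry and COVID-19, and the Protocol already warns that a change in the later period is likely due to unobserved confounders.
- *Counting one admission for both outcomes is an error in itself.* The outcomes are modelled separately, and a COPD admission with a true pneumonia code may properly count for both. The objection is only to overlap without a pneumonia code.
- *Deleting J22 would make the two lists match.* It would make every label name pneumonia. J85.1, lung abscess with pneumonia, also has no evident ICD-9 counterpart in the printed list.

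**Conclusion.** The point holds as a specificity defect in the definition of the primary safety outcome. Applied as written, the ICD-10 list counts admissions with J22 and no pneumonia code as pneumonia hospitalizations. These include some that are severe exacerbations by the Protocol's own definition. The likely consequence is some attenuation of the safety hazard ratio. That direction assumes that J22-only admissions are less affected by the choice of device than pneumonias are, and that misclassification is similar in both arms.

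The presence of the code is certain, but its effect is not. The illustrative shift from 1.20 to about 1.19-1.16 rests wholly on the assumed 5-15% share and the assumed J22-only hazard ratio of 1.0-0.9. A reader might infer that exacerbation admissions substantially contaminate the endpoint, but the Protocol gives no frequency that would show this. The correction is worth making because it is cheap and is best settled before results are seen. The contradiction about the study period needs correcting whatever is decided about J22.

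**What to change.** - Delete J22 from the primary safety definition and from every analysis built on the same list, such as the annual rate of pneumonia hospitalizations and sensitivity analysis 7 where they share it. Every remaining code then names pneumonia. If the investigators want to retain J22, use it only in an added sensitivity analysis.
- Reword the sentence on code conversion to say that the study spans both coding systems, with ICD-9 codes used for earlier claims and the converted ICD-10 codes for later ones.
- Leave the PPV wording as it is.

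The cost is one code removed from one measure, one sentence rewritten and a re-run. The event count would fall slightly, with a correspondingly small loss of precision.
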